### Methods: monitoring

#### Data monitoring

In order to monitor the trial process and participants’ safety, a trial steering committee (TSC) was established to make sure the trial run well. The members of this committee are experts from different professional fields, including hypertension management, cardiovascular disease, biostatistics and other fields. All personnel from the committee are absolutely independent from and have no competing interests with the funders and sponsor. We invited the staff from the Clinical Trial Institution of Jiangsu Province Hospital, and School of Public Health, Nanjing Medical University to regularly monitor the data and report to the committee. The TSC will meet onsite at each study site every three months to track the trial process and monitor the participant’s safety.

#### Harms and auditing

In this study, potential risks of PFM therapy are the thermal damage of local skin, subcutaneous tissue, and organs adjacent to perirenal fat. Any discomforts or abnormal indicators changes through energy emission path including skin, muscles, renal area, and intestine will be identified as adverse events (AEs) and will be recorded in eCRF and EDC system with details of onset time, severity, and duration. The severity of AEs and their correlations with PFM therapy will be carefully evaluated in accordance with the Common Terminology Criteria for Adverse Events [17]. Severe adverse events (SAEs) included deaths, life-threatening disease or injury, permanent damage to body structure or function, and diseases requiring hospitalization treatment that are determined by the investigator according to the principles of GCP. Investigators are responsible for dealing with the SAEs to protect the participants as much as possible and reporting the SAEs to the local ethics committee within 24 h. AEs will be reported within 3 days after each visit. All adverse events will be revealed in the trial publication. And the trial will be audited onsite periodically.

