### Sham procedure

Patients who are assigned to the sham control group share the same procedure as PFM does except that the focused ultrasound will not transmit energy.

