### Criteria for discontinuing

Participants may discontinue this trial for any of the following reasons:• They may choose to withdraw for any reason• They have severe side effects that require unmarking to get cured• Their blood pressure is within “escape criteria,” defined as office SBP ≥ 180mmHg or < 90 mmHg• They have a significant deviation from the study algorithm, e.g., changing the established antihypertensive drugs scheme• Any other rational reasons to withdraw from the study

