### Outcomes

We speculate that PFM will have a significant blood pressure lowering effects compared with the sham-control group. The endpoints in the present study include primary endpoints, secondary endpoints, and safety endpoints.

Primary endpoint measure:• Changes in office systolic blood pressure at 1-month compared with baseline

Secondary outcome measures:• Changes in office blood pressure at 3 months compared with baseline• Changes in mean systolic blood pressure measured by 24-h ambulatory blood pressure monitoring at 1 month compared with baseline• Changes in mean systolic blood pressure measured by 24-h ambulatory blood pressure monitoring at 3 months compared with baseline• Changes in the heart rate at 1 month compared with baseline• Changes in the mean heart rate measured by 24-h ambulatory blood pressure monitoring at 1 month compared with baseline

Safety endpoint measures:• Any severe adverse events (SAE) related to the intervention. The SAE was defined as acute renal failure, acute intestinal perforation, and thromboembolic events, etc.

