### Statistical method

For the primary endpoint, a mixed-effect model for repeated measures (MMRM) adjusted with baseline office SBP will be used to compare the group difference of the office SBP changes from baseline to 1 month. For the secondary endpoint, we will also use the MMRM method adjusted with mean SBP or heart rate to assess the changes in the mean SBP or heart rate from baseline to each visit point. And LS-means method adjusted with baseline SBP or heart rate will be used to estimate the changes in SBP or heart rate and 95% confidence intervals. Imputation for missing values of the main indicator will be conducted using the Markov chain Monte Carlo (MCMC) model which will be performed as the result of the sensitive analysis. We predefine an adverse event of laboratory index that is significantly abnormal at follow-up compared with baseline. Detailed presentation of adverse events will be described and explore the relationship with PFM products. The efficacy analyses will be carried out based on the full analysis set and the pre-protocol set. All baseline characteristics analysis will be conducted on the basis of the full analysis set. The safety evaluation will be analyzed from the safety analysis set. A two-sided *P* < 0.05 will indicate significance in all statistical analyses used by the SAS software V.9.4 (SAS Institute, Cary, NC).

An interim analysis is planned when 50 subjects (100 subjects in total) are enrolled in each group and completed 1 month follow-up, which will be conducted by an independent data monitoring committee (IDMC). The purposes of the interim analysis are as follows: (1) to evaluate the safety (a necessary disruption of the study is considered when there are serious or expected adverse events) and (2) to assess the efficacy. This trial will be expected to terminate in advance if the hypothesis test *P* value is less than the boundary value of the interim analyzed *α* for the primary endpoint. And if the *P* value is greater than interim analyzed *α* with statistical power less than 60%, re-estimating the sample size is needed to make the final statistical power greater than 80%. In accordance with O’Brien-Fleming method, the interim analyzed *α* = 0.005, and final *α* = 0.048.

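### Read literally, the adverse event definition is tied to the ultrasound energy path, so non-serious blood-pressure, heart-rate and ECG events fall under no definition

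*Protocol article*

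**What the plan says.** Four places in the protocol article bear on what counts as an adverse event.

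- **Harms and auditing, general definition.** "Any discomforts or abnormal indicators changes through energy emission path including skin, muscles, renal area, and intestine will be identified as adverse events (AEs". The sentence before it frames the risk as local: "potential risks of PFM therapy are the thermal damage of local skin, subcutaneous tissue, and organs adjacent to perirenal fat".
- **Statistical method, laboratory rule.** "We predefine an adverse event of laboratory index that is significantly abnormal at follow-up compared with baseline". This has no limit of location.
- **Harms and auditing, severe events.** "Severe adverse events (SAEs) included deaths, life-threatening disease or injury, permanent damage to body structure or function, and diseases requiring hospitalization treatment". These are defined by outcome, again with no limit of location.
- **Outcomes, safety endpoint.** "The SAE was defined as acute renal failure, acute intestinal perforation, and thromboembolic events, etc".

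Blood-pressure extremes appear elsewhere. Criteria for discontinuing lists, as a reason to leave the trial, an office SBP of at least 180 mmHg or below 90 mmHg. It does not say whether reaching either limit is also an adverse event.

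**The concern.** The general definition sorts events by where they occur. That suits thermal injury. It does not suit harms that would follow from the intended effect. The treatment is meant to lower blood pressure, and heart rate is a secondary endpoint (Outcomes). Participants enter on one to three drug classes (Eligibility criteria), which are expected to stay unchanged for the 3 months of follow-up (Intervention). Low blood pressure, a slow heart rate and related symptoms are therefore foreseeable, and none of them is a finding in the skin, muscles, renal area or intestine.

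Two uses of the data are at stake. Harms and auditing promises that the publication will disclose all adverse events, and this can cover only what meets the definition. The interim analysis, planned once 100 participants have completed 1 month, has safety as its first purpose, and it too would work from the restricted set.

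**Working it through.** No figure in the documents bears on this point, so there is nothing to recompute. The check is to take each kind of event and ask which stated definition covers it.

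| Kind of event | Path definition (Harms and auditing) | Laboratory rule (Statistical method) | Severe event (Harms and auditing; Outcomes) | Covered? |
|---|---|---|---|---|
| Skin or muscle injury at the treated site | yes | – | if serious | yes |
| Significantly abnormal blood or urine result | – | yes | if serious | yes |
| Syncope leading to admission | – | – | yes, hospitalization | yes |
| Thromboembolic event | – | – | yes, named in Outcomes | yes |
| Dizziness or symptomatic hypotension, not serious | depends on how the sentence is parsed | – | no | unclear |
| Low blood pressure, bradycardia or abnormal ECG without symptoms, not serious | no | no, not a laboratory index | no | no |

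**The unclear row.** The general definition can be parsed in two ways.

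1. The path limit applies to both discomforts and abnormal indicators. Dizziness is then not an adverse event.
2. The limit applies to abnormal indicators only. Any discomfort then counts, and dizziness is an adverse event.

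The text does not settle which is meant. With three sites recording, the same complaint could be entered at one and not at another.

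**The last row.** Neither parse helps. An abnormal blood pressure, heart rate or ECG without discomfort is an indicator, and under both readings an indicator must lie on the path. The list of tissues is introduced as examples and is not closed, but it can extend only to other tissues on the path.

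**Would these events be seen?** Yes, in part. Table 1 schedules office blood pressure at days 1, 14, 30 and 90, and ambulatory monitoring and ECG at days 1, 30 and 90. Abnormal values at those visits would be in the database. What is missing is a rule that makes them adverse events. Episodes between visits have no scheduled measurement to reveal them.

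**The case against.** The strongest case against has four parts.

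- **The gap is narrower than it may look.** A reader might infer that systemic harms in general are excluded. They are not. Laboratory abnormalities and serious events count wherever they arise, so serious blood-pressure and heart-rate events are covered. Thromboembolism is named as a severe event in Outcomes. This stands, and it limits the point to non-serious, non-laboratory events off the path.
- **The sham arm is not shown to be excluded.** Because sham participants have the same procedure "except that the focused ultrasound will not transmit energy", a reader might infer that local events could not qualify in that arm and would be recorded unequally. The documents do not support this. The path followed by a list of tissues reads naturally as anatomy, which every participant has. Adverse events are recorded at each visit (Trial design). Follow-up staff are blinded, and the question about discomfort after the procedure is not limited by arm (Blinding). What remains is that wording built on emitted energy would be better made arm-neutral.
- **The measurements are not lost.** Blood pressure and ECG are scheduled in both arms, and reasons for discontinuing follow-up are recorded (Data collection at the final visit). This is true, and it makes the problem largely one of classification. But adverse event tables and a safety review are built from classified events.
- **This is a condensed article.** The full protocol may say more. Yet the article states a rule rather than leaving one out, and the rule as stated is too narrow.

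It could also be argued that locating an event on the path prejudges its cause. That goes too far: Harms and auditing evaluates correlation with the therapy as a separate step.

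**Conclusion.** The point holds in limited form. Taken literally, the stated definitions together leave non-serious, non-laboratory events off the energy path under no adverse event rule, and the general definition is ambiguous about discomforts. In a trial of a blood-pressure-lowering intervention on unchanged drugs, these are foreseeable harms, so the safety comparison could be incomplete.

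The scope is this one class of events, in both arms, over 90 days in a planned 200 participants. No number of missed events can be given: the documents state no rate of symptomatic blood-pressure or heart-rate events, and any percentage would be a guess. Nor do they show bias between the arms; incompleteness in both is the supported conclusion.

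The verdict assumes that site staff follow the wording as printed and that the full protocol does not define adverse events more broadly. It deserves correction because the remedy is specific and cheap.

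**What to change.** Reconcile the definitions in Harms and auditing and Statistical method into one: any untoward medical occurrence after the procedure, in either arm, whatever its location or presumed cause. Assess relatedness to the procedure afterwards, as a separate step. Keep findings along the energy path (skin, muscle, renal area, intestine) as adverse events of special interest within that definition. State how reaching either blood-pressure limit in Criteria for discontinuing is recorded for safety reporting. This concerns recording only and leaves the limits and their clinical handling untouched.

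The cost is protocol and eCRF wording, ethics re-review of the revised protocol (Ethics and dissemination), and more unrelated minor events to record and code. Recruitment had already reached 74 by February 8, 2022 (Trial status), so participants enrolled before the change will have been recorded under the present wording. The report should say so and, where source records allow, their earlier visits should be re-read against the new definition.

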#### Ethics and dissemination

This study protocol was comprehensively considered and will not be amended easily without written permission from the Ethics Committee of the responsible unit. The revised protocol will be inspected by the local ethical boards again. The informed consent approved by local ethical boards will be presented to the potential participants and their authorized surrogates. Investigators is responsible for introducing the study design, procedure, potential harms, and benefits, and answering the participant’s questions. The participant can only be enrolled after signing their name on the page of the informed consent form. Additional sample collection is also noted on the pages of informed consent. For each visit, 5 ml blood samples and 2 ml urine samples will be collected and stored. To protect participants’ confidentiality, private information, including names, addresses, contact, and identified numbers will be kept within each investigation center. Access by any third party will be prohibited. All data used for analysis and report shall not have personal identifiers except for unique screening codes or randomization codes. Once the AEs occur, medical care will be provided for participants promptly. In addition, appropriate assistance and management will be presented according to the relevant laws and regulations.

The study results will be published in peer-review journals, presented at scientific conferences, and shared with all participants. Access to all deidentified data will be permitted only for certificated researchers with written approval from the responsible investigators. Any data required to support the protocol can be supplied on reasonable request.

## Discussion

Epidemiological studies have demonstrated that perirenal fat is closely associated with elevated blood pressure [8, 9]. It is reported that accumulation of fat in the renal sinus may promote hypertension due to compression of the lymphatic and venous vessels by perirenal fat, leading to activation of the renin-angiotensin-aldosterone system [18]. However, observational studies failed to clarify the pathological mechanism of hypertension caused by perirenal fat. Recently, researchers found that bilateral perirenal fat ablation leads to a long-term reduction of high blood pressure in spontaneously hypertensive rats and has no influence on normal blood pressure in control rats; they further indicate that perirenal afferent nerves serve as a pathological node of hypertension that sustains elevated blood pressure via suppressing CGRP, thereby being a potential therapeutic target to tackle primary hypertension [10]. And the perirenal fat is so distinguished that no other fat pad such as inguinal, pararenal, or epididymal adipose tissue is associated with the maintenance of high blood pressure in their research. Moreover, perirenal fat, especially the fat pad in the lower pole of the kidney, is a relatively independent solid tissue, which is different from other visceral fat, making it a potential target for clinical intervention to lower blood pressure.

Long-term use of medical treatment is the essential method for hypertensive patients, which is bound to have increased risks of adverse events. Especially for those who are resistant to antihypertensive drugs, traditional medical therapy is of little help. Therefore, novel therapeutic methods are urgent for lowing blood pressure, notably the instrument treatment for hypertension. Renal denervation (RDN) is an intervention that uses an ablation catheter to destruct sympathetic nerves of renal arteries, which might be a promising way to reduce blood pressure for individuals with resistant hypertension. Several randomized clinical trials with unblinded designs showed remarkable effects of RDN on lowering blood pressure and few complications [19, 20]. However, further RCT with a sham-control design presented a similar blood pressure reduction between the RDN group and the sham control group, indicating the placebo effects of RDN [21]. Even though a series of RCTs confirmed the effectiveness of RDN on elevated blood pressure after optimizing the criteria of the enrollment and working mode of the ablation catheter [22, 23], physicians are still concerned about the safety of RDN since it is an invasive procedure. Hence, a noninvasive way is needed to reduce blood pressure. Perirenal fat has become an ideal target for noninvasive intervention using focused power ultrasound. We previously conducted a small sample size study revealing that PFM therapy was a safe and effective way to lower blood pressure for individuals with essential hypertension [24].

Traditional focused power ultrasound has limited use on adipose tissue in the abdominal cavity. In order to equip a focused power ultrasound dedicated to the intervention of perirenal fat, we designed and developed a novel machine that can be effectively and safely used for the modification of perirenal fat. This novel FPU machine has the strength of temperature monitoring of the target area and personalized output power according to the fat characteristics of the subjects to ensure that the target perirenal fat can be effectively and safely modified.

To our knowledge, the present study is the first to use noninvasive FPU to intervene in perirenal fat to achieve the goal of reducing blood pressure for patients with essential hypertension. Our study is expected to provide a new treatment strategy to control high blood pressure. At the initial stage, we are exploring the efficacy of this new strategy for hypertensive patients on medication with mild to moderate elevated blood pressure. In the future, we will expand the population for adaption of this new therapy, such as new onset hypertensive patients, hypertensive patients without taking medications, and even refractory hypertensive patients.

## Trial status

This paper is in accordance with the protocol (version 1.3.1, data 23 August 2021). The study recruitment began on November 1, 2021, with 74 participants recruited by February 8, 2022, and is estimated to complete the study on September 30, 2023.

## Data Availability

The investigators will have access to the final trial data and material. Any other access to data without written approval from the responsible investigator is prohibited.
